### Proprioception

The participants’ knee proprioceptive range of motion will be measured using an electrogoniometer (Ergotest Technology, Norway; range: 15–320°). The use of an electrogoniometer for measuring the relative position of the knee joint has been shown to be a reliable method for assessing joint proprioception [57]. To measure the proprioceptive range of motion, the participants will be asked to wear shorts for ease of attachment of the electrogoniometer to the knee joint [58]. The participants’ eyes will be blinded to eliminate visual feedback. They will be asked to sit on a high plinth with the hip at an angle of 80° flexion in such a way that the distal hamstrings and knee joint are hanging freely at a resting position of 85° knee flexion. A thin foam will be wrapped around the tested knee to minimize cutaneous sensation feedback from the attachment of the electrogoniometer [59]. While keeping the knee in a neutral position, the electrogoniometer will be placed on the lateral side of the knee joint and its axis coinciding with the flexion/extension axis of the knee [60]. The goniometer will be kept in place using an elastic strap wrapped around the cushion padding. Participants will be instructed to bend the knee to a resting position of 85° of flexion and in this position, they will be instructed to bend from the resting position to the target angle (TA) of 70° and hold there for 5 s, then return to the resting position (85° of flexion) [61, 62]. The participants will be then asked to repeat the procedure of bending the knee from the resting position of 85° and say “YES” on perceiving they reached the target position of 70° and hold. This angle will be noted on the electrogoniometer and documented as the perceived angle (PA). The difference between TA and PA is the absolute angular error (AAE), which will be documented [61]. This procedure will be repeated three times and the average of the three readings will be calculated and recorded as the error for each participant [57]. The inter-rater (between assessors) and intra-rater (within assessors) reliability of the electrogoniometer used in the present study will be evaluated.

### Quality of life

The quality of life of the participants will be measured using the mini Osteoarthritis Knee and Hip Quality of Life Questionnaire (OAKHQOL) [63]. It is a 20-item questionnaire derived from the original 40-item questionnaire developed by Rat et al. [64]. The questionnaire consists of five dimensions subscales: physical activities, mental health, pain, social support, and social functioning; and three independent items addressing sexual life, professional life, and fear of being dependent. Each item is measured on a numerical rating scale from 0 to 10 and the mean item score becomes the corresponding dimension score [63]. The mini OAKHQOL has been shown to have adequate internal consistency (0.78–0.95), test-retest reliability (ICC = 0.66–0.89), and factorial validity in subjects with knee and hip OA [65].

As no Hausa versions of the KOS-ADLS and OAKHQOL are available for use, these questionnaires will be translated from English into Hausa language using guidelines for the process of cross-cultural adaptation of self-report measures [66]. This is to ensure that reliable data is collected and participants who are unable to complete English measures are not excluded in the trial [54]. However, English versions of IKHOAM, VAS-pain, KOS-ADLS, and OAKHQOL will be applied to those willing to respond in English.

### Adverse events

Based on the findings of our pilot study (unpublished data), no serious adverse events were reported with the KBA exercise training program. However, all participants will be informed during recruitment of the possibility of experiencing common adverse events related to exercise interventions such as muscle pull, soreness, or cramp. They will be educated that these symptoms are temporary and self-limiting. Nonetheless, in case of any serious adverse events such as exacerbating joint pain, discernible joint swelling, and excessive fatigue, they will be advised to report such events immediately to the primary investigator or treating therapists for assessment and prompt action. Any adverse events will be recorded and reported to the research ethics committee of Aminu Kano Teaching Hospital, or National Orthopaedic Hospital Dala, or Kano State Ministry of Health, Nigeria.

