### Interventions

Participants in the conventional physiotherapy group will receive brief patient education, ultrasound therapy, and stretching and strengthening exercises. The program will be delivered twice weekly for 8 weeks except for the education program which will be provided in two sessions. The stretching exercises will be performed as warm-up and cool-down. Participants in the twice-weekly KBA group will receive two sessions per week of the KBA exercise training for 8 weeks whereas participants in the thrice-weekly KBA will receive three sessions per week of the same exercise training as for the twice-weekly KBA group. Both the two KBA exercise training groups will receive the same intervention program as described for the conventional physiotherapy group prior to receiving the KBA exercise  training. All exercises will be delivered individually under the supervision of the treating physiotherapists. All lower-extremity exercises will be performed bilaterally. The participants will be instructed to perform exercises consistent with their group allocation two times per day at home to encourage self-management. They will be encouraged also to perform a walking exercise of 30 min per day at least 3 to 4 days per week at home. To enhance compliance with the home program, a leaflet with descriptions and pictures of the exercises will be provided to the participants. However, exercises that are more challenging or those requiring the strict supervision of the therapist will be not advised for the home program.

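### Expected symptoms of knee OA under exercise are given as examples of serious adverse events without a seriousness criterion, and the only reporting route stated runs through contacts that differ by arm

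*Protocol article*

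**What the plan says.** The Adverse events section uses two groups of events. The first is "common adverse events related to exercise interventions such as muscle pull, soreness, or cramp", and about these participants hear the following: "They will be educated that these symptoms are temporary and self-limiting". The second group is introduced with "in case of any serious adverse events such as exacerbating joint pain, discernible joint swelling, and excessive fatigue"; for these, "they will be advised to report such events immediately to the primary investigator or treating therapists for assessment and prompt action". The section adds: "Any adverse events will be recorded and reported to the research ethics committee". It also reports from the unpublished pilot that "no serious adverse events were reported with the KBA exercise training program". It states no criterion that makes an event serious, and no time or method at which all participants are asked about harms.

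The sections on stretching and strengthening exercises and on KBA exercises both foresee that a patient may report a worsening of symptoms during training. Both say what then happens to the exercise, and neither calls the event serious.

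Under Interventions, the conventional programme and the twice-weekly KBA programme each run twice a week for 8 weeks, while the thrice-weekly arm receives "three sessions per week of the same exercise training". Under Randomization and blinding, the treating physiotherapists are not blinded and the outcome assessors are.

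**The concern.** Seriousness normally refers to the consequence of an event: death, threat to life, hospital admission or lasting disability. The three printed examples describe symptoms by their intensity, and none of them meets such a criterion by itself. Pain is also a secondary outcome of the trial, and pain and swelling are symptom items of the KOS-ADLS, so ordinary fluctuation in the disease could enter the serious-event count. A reader of the results could not tell a hospital admission from a sore, swollen knee. The pilot statement has the same ambiguity.

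The second part concerns how events come to light. The trial asks which KBA frequency is better, and a reader will want to weigh benefit against harm by arm. If harms are learned mainly through contact with the treating therapists, and that contact varies with frequency, the two arms at the centre of the question are observed unequally.

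**Working it through.** **The label.** Three places in the protocol article, side by side:

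- Adverse events: worsening joint pain is an example of a serious event.
- Stretching and strengthening exercises: a reported worsening of symptoms is foreseen during training and is not called serious.
- Kinesthesia, balance and agility exercises: the same.

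One kind of event is thus serious in one section and a foreseeable event of training in two others. With no criterion stated, nothing in the article settles which applies when events are counted.

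**The reporting route.** The advice to report attaches to the events called serious. For the common events the article states no route, only the reassurance that they pass. The sentence that any adverse events are recorded covers both groups but does not say how they become known.

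**Scheduled contacts.** Sessions = sessions per week × 8 weeks.

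- Conventional: 2 × 8 = 16, which reproduces the sixteen sessions stated in the Abstract.
- Twice-weekly KBA: 2 × 8 = 16.
- Thrice-weekly KBA: 3 × 8 = 24.

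The Interventions section places KBA after the conventional programme. I read this as the same visit, although it is not said outright. On that reading:

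- Treatment sessions only: 24/16 = 1.50.
- With the four post-baseline assessments common to all arms (post-intervention, 3, 4 and 6 months): (24 + 4)/(16 + 4) = 28/20 = 1.40.

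If KBA were given at separate visits, the arms would have 16, 16 + 16 = 32 and 16 + 24 = 40 treatment visits. The thrice-weekly arm would then have 40/32 = 1.25 times the visits of the twice-weekly arm and 40/16 = 2.50 times those of control. Contact is unequal on either reading.

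**What unequal contact could do.** The documents give no event or reporting rate, so this is an illustration under assumptions. Let q be a constant, independent probability that a report is made at any one treatment session, with no reporting elsewhere. The chance of at least one report is 1 − (1 − q)^16 or 1 − (1 − q)^24.

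| Assumed q | 16 sessions | 24 sessions | Ratio |
|---|---|---|---|
| 0.5% | 7.7% | 11.3% | 1.47 |
| 1% | 14.9% | 21.4% | 1.44 |
| 2% | 27.6% | 38.4% | 1.39 |
| 5% | 56.0% | 70.8% | 1.26 |
| 10% | 81.5% | 92.0% | 1.13 |

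The direction is the same throughout. The sizes are not estimates for this trial: the model leaves out reporting between sessions, which the article invites, and it does not separate the occurrence of an event from its detection.

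**The case against.** The case against has real force on the second part. A reader might infer that events are collected only when volunteered. The text does not say so: it states one route, says that any adverse events are recorded, and is silent on active questioning, which a condensed article may leave to the full protocol. A reader might also infer that the thrice-weekly arm has 50% more chances to report. That figure covers scheduled treatment sessions only, whereas participants in every arm are advised to report at once, at any time, and all arms do home exercise between sessions. The eight extra sessions (24 − 16) are also real extra exposure, so an excess of events in that arm could be a true dose effect. The Statistical analysis section describes no between-arm test of adverse events, and pain is already measured at the same times in all arms by blinded assessors.

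On the label, the three symptoms are examples in advice to participants and not an analysis definition. No count exists yet, and since all events are to be recorded whatever they are called, they can be reclassified.

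All of this stands as a limit on the claim. It does not remove two facts: the printed examples point away from any usual meaning of serious and conflict with the exercise sections, and the one route stated runs to the investigator or to unblinded therapists whose scheduled contact differs by arm. Extra exposure and extra detection cannot be separated unless harms are also asked about in a common way.

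**Conclusion.** The labelling point holds on the article's own text: a serious-event count made under this wording would be inflated by expected symptoms and could not be interpreted. To say that the count is already wrong would go too far, because none has been made and the events can still be reclassified.

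The ascertainment point holds as a risk. Any comparison of adverse-event frequency between arms could mix detection with exposure. The imbalance in scheduled contact is 24 against 16, or 28 against 20 with the common assessments, provided that KBA and conventional care share a visit. The resulting distortion cannot be derived from the documents, and the illustrated ratios of 1.13 to 1.47 rest wholly on assumed reporting probabilities.

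The planned efficacy outcomes are not affected. This is a minor point that is cheap to correct.

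**What to change.** 1. Relabel the three symptoms as adverse events of interest, and reserve the word serious for a stated seriousness definition. Recruitment has run since February 2018, so reclassify events already recorded before analysis. State which meaning applied to the pilot result.
2. Leave the advice on immediate reporting unchanged. Add one adverse-event question, worded identically in all arms, at the existing post-intervention, 3-, 4- and 6-month assessments.
3. Base any between-arm summary of harms on those answers, and list events volunteered between assessments separately. For participants already past some of these assessments, say that the common question was not asked.

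The cost is one definition and one item on an existing form, about a minute per visit, with no extra staff. There are two small downsides. Participants must recall events over the interval between assessments. An answer about exercise-related harm could also disclose the allocation to the blinded assessor; a self-completed form, filled in after the outcome measures and kept from the assessor, limits this.

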### Sample size estimation

Based on the results of our pilot study (unpublished data), using the effect size of 0.185 for between-group difference in the primary outcome (physical function measured by IKHOAM), a priori sample size was calculated assuming a statistical power of 90%, an alpha of 5% (two-tailed), and an effect size of 0.47. The calculations suggested a sample size of 102 would be needed. However, while anticipating a 20% attrition rate (*n* = 20), a total sample size of 120 will be needed with 40 participants per group. The calculations were performed with the G-power 3.1.9.2 software (University of Dusseldorf, Dusseldorf, Germany) [67].

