### Randomization and blinding

After completing the baseline assessment, the participants will be randomized into three intervention groups; twice-weekly KBA, thrice-weekly KBA, and conventional physiotherapy (control) in the ratio of 1:1:1. The randomization will be performed using an online randomization generator (http://www.randomization.com) by utilizing block randomization with a block size of 3 and 6. A third party not  involved in the study will perform the randomization process. Allocation of participants will be concealed using consecutive numbered, sealed, and opaque envelopes. The outcome assessors (physiotherapists) will be blinded to the group allocation and will not be involved in administering the interventions. The participants will be told they are in a “twice weekly KBA” or “thrice-weekly KBA” or “conventional physiotherapy,” but the type of intervention will not be specified. Conversely, due to the nature of the interventions, it will be difficult to blind the physiotherapists providing the treatments. Unbinding conditions will be only permissible when there is a medical emergency.

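### The sample-size figures disagree: 120 randomised with 20% attrition leaves 96, below the stated 102, and no test fitting this design was found to give 102 from an effect size of 0.47

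*Protocol article*

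**What the plan says.** All the figures are in one paragraph of the Protocol article, under Sample size estimation.

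- The pilot, which is unpublished, is the source: "using the effect size of 0.185 for between-group difference in the primary outcome".
- The same sentence then gives the calculation 90% power, a two-tailed alpha of 5%, and "an effect size of 0.47". Neither effect size has a named metric.
- The result before attrition: "The calculations suggested a sample size of 102 would be needed".
- The attrition step: "anticipating a 20% attrition rate", printed as n = 20, so that "a total sample size of 120 will be needed with 40 participants per group".
- G-power is named as the software, but not the test chosen in it.

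Elsewhere, Randomization and blinding sets three arms: "twice-weekly KBA, thrice-weekly KBA, and conventional physiotherapy (control) in the ratio of 1:1:1". Outcome assessments and follow-ups lists five assessments. Statistical analysis plans a mixed between-within ANOVA with group, time and group-by-time effects.

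**The concern.** Two steps can be checked from the printed numbers, and neither checks out.

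The first is the attrition allowance. An inflated sample should return the required number once the expected loss is taken off, and 120 does not do so.

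The second is the requirement itself. With the stated power and alpha, 0.47 should lead to 102 by some test that belongs to this design. The obvious candidate gives a much smaller number.

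At stake is whether the planning claims (the effect targeted, the power and the loss the trial can absorb) can be relied on as printed. If 102 is not the 90% figure for the planned test, either the power or the target effect is misreported.

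**Working it through.** **Inputs.** From Sample size estimation: effect sizes 0.185 and 0.47, power 90%, alpha 0.05 two-tailed, requirement 102, attrition 20% (n = 20), total 120. From Randomization and blinding: 3 arms, 1:1:1. From Outcome assessments and follow-ups: 5 time points.

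**1. The attrition step.** This needs no assumption about the test.

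- The printed n = 20 matches 20% of 102: 0.20 × 102 = 20.4.
- Adding it gives 102 + 20 = 122, not 120.
- Completers from 120 at 20% loss: 120 × 0.80 = 96, or 32 per arm. The shortfall is 102 − 96 = 6.
- Number needed to keep 102: 102 / (1 − 0.20) = 127.5, so 128, or 129 (43 per arm) in equal arms.
- Loss that 120 can absorb: (120 − 102) / 120 = 18/120 = 15%.

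**2. How the two effect sizes may be linked.** If 0.185 is an eta-squared, Cohen's f = √(0.185 / (1 − 0.185)) = √(0.185 / 0.815) = 0.476, close to 0.47. This is an inference from one numerical match; the article does not say so.

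**3. Trying to reproduce 102.** For an F test with numerator df u, 3 groups and total N, power = P[F(u, N − 3; λ) > critical value], with λ = f²N. At f = 0.47, alpha 0.05 and 90% power:

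| Numerator df | Effect in this design | N needed |
|---|---|---|
| 2 | group | 61 (63 in equal arms) |
| 4 | time | 75 |
| 8 | group × time | 94 |
| 10 | none | 102 |

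With 15 design cells instead of 3 groups, the 8-df figure is 96. The df available here are group 3 − 1 = 2, time 5 − 1 = 4, and interaction 2 × 4 = 8.

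Other options tried with 0.47 at the stated alpha and power:

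- Repeated-measures ANOVA over several numbers of visits, correlations and effect-size conventions: 15 to 58 for the group effect and 7 to 64 for the interaction.
- Approximate MANOVA for group × time with five visits: 91.
- Two-sample t test, reading 0.47 as Cohen's d: 97 per arm.

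None gives 102.

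**4. What the figures imply for power (one-way group F test, 3 groups).**

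- f = 0.47: 99.1% at N = 102 and 98.7% at N = 96.
- If 102 is to give exactly 90%, f must be 0.358, an eta-squared of 0.358² / (1 + 0.358²) = 0.113. Then N = 96 gives 88.0%.

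**The case against.** Several things can be said for the plan, and most of them stand in part.

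- **A reader might infer that 0.47 cannot give 102 at all.** It can: a fixed-effects F test with 10 numerator df returns exactly 102. That may be how the number arose, for example through a mistaken df entry, but the article does not say. The supportable statement is that no test fitting this design was found to give it.
- **A reader might infer that 0.185 and 0.47 contradict each other.** They need not, since an eta-squared of 0.185 converts to f = 0.476. What is missing is the labels, and a condensed article may leave those, and the choice of test, to the full protocol. That would not repair the attrition arithmetic, where every figure is printed.
- **A reader might infer that the trial is underpowered.** Read as Cohen's d, 0.47 would give only about 46% pairwise power with 32 per arm and 48% with 34, before any Bonferroni correction. The documents do not support choosing that reading; the match between 0.185 and 0.476 points to f.
- **A reader might infer that a null result could not be interpreted.** That does not follow. Omnibus power is about 88% to 99% under the one-way readings above, and interpretation will rest on the estimates and their intervals.
- **The intention-to-treat analysis uses multiple imputation, so all 120 are meant to be analysed.** This is correct, and 96 describes completers. Imputation does not restore the information lost, so the allowance still needs correcting.

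**Conclusion.** The paragraph is wrong as written on the attrition step, with no assumption needed: 120 covers 15% loss, not 20%, and at 20% it leaves 96 completers against a stated need of 102.

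The 102 is also not the 90% figure for any effect of this design that could be found from 0.47. If 0.47 is Cohen's f, it is well above the 61 (63 in equal arms) needed for the group effect, and above the 94 to 96 for an F test with the interaction's 8 df. That conclusion rests on the inferred metric and on the set of tests tried.

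The practical effect on power is modest. For the one-way group test, power at 96 is 98.7% if f = 0.47, and 88.0% if 102 is the true 90% target. The error lies in the stated planning figures; nothing here shows that the trial needs more patients.

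**What to change.** Keep 120 and rewrite the paragraph:

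1. The authors state the metric of 0.185 and of 0.47, how one was obtained from the other, and the G-power test and degrees of freedom actually used. These should come from their records and not be assumed from the numerical match.
2. Replace 102 with the number that test gives, or state the effect size to which 102 corresponds (f = 0.358 if the test was a one-way F test).
3. State either that 120 leaves 96 completers (32 per arm) at 20% attrition, or that 120 covers 15% attrition for 102.
4. Give the power at 96 for the named test. For a one-way test this is 98.7% if f = 0.47, or 88.0% if 102 is the 90% target.

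The cost is one reworded paragraph and a look back at the original calculation. No patients are added. The stated attrition allowance or completer number becomes slightly less favourable.

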### Statistical analysis

An independent statistician who will be blinded to the study procedures will conduct all statistical analyses. The normality test of the data will be verified with the Shapiro–Wilk test and visual inspection of distribution plots. To account for potential missing data in datasets, per-protocol (PP) and intention-to-treat (ITT) approaches will be considered for the data analysis. For the PP approach, only participants who completed all treatment sessions will be included in the analysis. For the ITT approach, multivariate imputation by chained equations will be employed [68]. Descriptive statistics of mean and standard deviation will be used to summarize all continuous variables while frequency and percentages will be used to summarize all categorical variables. Mixed between-within subject ANOVA will be used to assess interaction effect (group x time), main effects for time, and between-subjects effect if the data is normally distributed. However, Friedman’s ANOVA and Kruskal–Wallis test will be used to analyze within-group change and between-group difference, respectively, if the data is not normally distributed. Post hoc analysis using Bonferroni correction will be conducted for any significant between-group difference observed. Effect size will be also computed to determine the magnitude of change in outcomes. All data will be analyzed using SPSS version 23 (IBM Co., Armonk, NY, USA) at an alpha level of 0.05.

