### Outcome assessments and follow-ups

The primary outcome will be physical function whereas the secondary outcomes will be pain intensity, knee stability, proprioception, and quality of life. Similar to previous trials on knee OA, if only one knee of the patient is affected, the evaluation of the outcomes will be done for this knee. If the patient has bilateral affectation of which only one meets the ACR criterion [48], only this knee will be evaluated. However, if the patient is having bilateral affectation according to the ACR criterion, the more painful knee will be selected for outcome evaluation.

All outcomes will be assessed pre-intervention, immediately post-intervention and at 3 months, 4 months, and 6 months post-randomization. Participants missing their regular appointments will be given makeup appointments until they reach the required sessions for each group. This will be done by contacting them through phone calls. All participants will be advised to refrain from other interventions during the trial except for those taking medications as prescribed by their physician and this information will be collected.

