## Discussion

There is evidence to suggest proprioceptive deficits in individuals with knee OA and that neuromuscular training programs targeting to improve proprioception are beneficial among these individuals [29–34]. The effectiveness of KBA as a proprioceptive training program in individuals with knee OA has been recently tested in clinical trials [36, 44–48], however, clinicians need to know the ideal dosage of KBA associated with the highest effectiveness as results of these previous trials were mixed. The present study will be aiming to determine the effects of a structured KBA exercise training program with different frequencies of treatment sessions (i.e., twice-weekly or thrice-weekly) on physical function, pain intensity, knee stability, proprioception, and quality of life in adults with knee OA. The outcomes will be evaluated at 8 weeks, 3 months, 4 months, and 6 months after randomization. We hope to follow-up the patients for a year if the 6-month follow-up results suggest this would be useful.

The findings of this study may provide evidence on the effectiveness of the KBA exercise training and the ideal number of sessions needed to achieve the highest effectiveness, which may guide clinical practice and minimize waste of time and resources.

Potential factors that could account for the limitations of the present study may include the lack of blinding of the treating therapists due to the nature of the interventions. Furthermore, because the present study is a multi-center trial employing the services of different treatment therapists with different skills and expertise, we cannot rule out the possibility of differential treatment. However, the assessor blind, three-arm RCT design with concealed allocation can be considered as the strengths of our study.

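### The mixed ANOVA leaves open which of two arm-comparing tests, and which visit, decides the trial, and it does not use baseline IKHOAM as a covariate

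*Protocol article*

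**What the plan says.** In the protocol article, the Outcome assessments and follow-ups section defines the primary outcome without a time point: "The primary outcome will be physical function whereas the secondary outcomes will be pain intensity, knee stability, proprioception, and quality of life". It then sets the schedule: "All outcomes will be assessed pre-intervention, immediately post-intervention and at 3 months, 4 months, and 6 months post-randomization". The Discussion repeats the follow-up times (the first given as 8 weeks) and ranks none of them.

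The Statistical analysis section fixes the model: "Mixed between-within subject ANOVA will be used to assess interaction effect (group x time), main effects for time, and between-subjects effect". If normality fails, "Friedman’s ANOVA and Kruskal–Wallis test will be used to analyze within-group change and between-group difference, respectively, if the data is not normally distributed"; that route names no visit either. The follow-on rule is "Post hoc analysis using Bonferroni correction will be conducted for any significant between-group difference observed". The significance level is set once, "at an alpha level of 0.05", and is not divided between tests. No covariate is mentioned.

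The Sample size estimation section gives the planning values, "assuming a statistical power of 90%, an alpha of 5% (two-tailed), and an effect size of 0.47", but names neither the test nor the visit they refer to.

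**The concern.** With five assessments, a group by time term and no covariate, the natural reading is that baseline is one of five levels of time. Three consequences follow.

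- **Open choice.** The time main effect does not compare arms, but the group by time and between-subjects effects both do. Either could be presented as the result, at whichever visit the post hoc comparisons favour. The Bonferroni step covers only the post hoc comparisons, not the choice between these two tests.
- **Dilution of one test.** The between-subjects effect averages over all visits, including the one taken before randomised treatment, where the expected arm difference is zero.
- **Lack of focus in the other.** The interaction is not shrunk by baseline, but it spreads the arm effect over (3 − 1) × (5 − 1) = 8 degrees of freedom and does not say when the arms differ.

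At stake are the error rate of the trial's main claim and, if the effect is smaller than planned, power that baseline data already being collected could supply.

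**Working it through.** **The plan's own figure.** The stated total before attrition is 102. If the pilot value 0.185 is read as partial eta squared, f = √(0.185/0.815) = 0.476, close to the stated 0.47. A one-way ANOVA with three groups, f = 0.47, 90% power and alpha 0.05 needs 63 in total. With five visits and correlations 0 to 0.9, the between-subjects factor needs 15 to 57 and the interaction 6 to 21. A two-sided t test with d = 0.47 needs 96 per arm. None gives 102, so the sample size does not reveal which test was meant to decide. That mismatch is a separate matter, and this point does not rest on it.

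**Type I error.** With complete data and equal correlations, the two arm-comparing F tests are independent under the null: 1 − 0.95² = 0.0975. A simulation of 8,000 null trials (N = 120, correlation 0.5) gave 0.098.

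**Inputs for power.**
- From the protocol: three equal arms, five visits, alpha 0.05, f = 0.47, and 120 randomised with 20% attrition, so N = 120 × 0.8 = 96 (32 per arm).
- Assumed, because the document gives no value: equal SD at all visits and a common between-visit correlation ρ of 0.3 to 0.8.
- Assumed smaller effect: arm means 0, 0.3 and 0.6 SD, so f² = (0.3² + 0 + 0.3²)/3 = 0.06 and f = 0.245, about half the planned 0.47.

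**Shrinkage.** A constant effect δ after baseline averages to (0 + 4δ)/5 = 0.8δ in the between-subjects test. An effect at one visit only averages to δ/5 = 0.2δ. For the interaction, the squared deviations of the visit profile from its own mean sum to 0.8² + 4 × 0.2² = 0.80 in both cases.

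**Noncentrality λ for a constant effect**, with values at N f² = 96 × 0.06 = 5.76 and ρ = 0.5:
- Between-subjects, 2 df: N f² × 0.64/[(1 + 4ρ)/5] = 5.76 × 0.64/0.6 = 6.14, power 58%.
- Interaction, 8 df: N f² × 0.80/(1 − ρ) = 5.76 × 0.80/0.5 = 9.22, power 54%.
- Baseline-adjusted test at one visit, 2 df: N f²/(1 − ρ²) = 5.76/0.75 = 7.68, power 68%.
- Baseline-adjusted mean of four post-baseline visits, 2 df: N f²/[(1 + 3ρ)/4 − ρ²] = 5.76/0.375 = 15.36, power 94%.

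**Power over ρ, constant effect, f = 0.245, N = 96:**

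| ρ | Between-subjects | Interaction | Adjusted, one visit | Adjusted, post-baseline mean |
|---|---|---|---|---|
| 0.3 | 72% | 38% | 59% | 94% |
| 0.5 | 58% | 54% | 68% | 94% |
| 0.7 | 48% | 80% | 85% | 98% |
| 0.8 | 44% | 95% | 95% | over 99% |

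**Effect at one visit only, f = 0.245, ρ = 0.5.** Between-subjects: λ = 5.76 × 0.04/0.6 = 0.38, power 8%. The interaction stays at 54% and the adjusted test at that visit at 68%.

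**The planned f = 0.47, N = 96.** If it holds at every post-baseline visit, between-subjects power runs from over 99% (ρ = 0.3) down to 95% (ρ = 0.8), and interaction power from 96% upwards. If it holds at one visit only, between-subjects power is 21% at ρ = 0.3 and 13% at ρ = 0.8.

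**The case against.** The strongest reply is that the power argument depends on an effect half the planned size and on a correlation that the document does not give. That stands: at f = 0.47 sustained over all follow-ups, both arm-comparing tests keep at least 95%.

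A reader might set 58% against 94% and infer a loss of 36 points from the planned analysis. That compares the weaker planned test with the strongest alternative. A baseline-adjusted test at a single visit has 68% at ρ = 0.5, a gain of 10 points over the between-subjects test. At ρ = 0.3 it has 59% against 72%, so it is weaker than the test it would replace. At ρ = 0.7 or 0.8 the interaction nearly matches or equals it. Only the post-baseline mean is clearly ahead at ρ up to 0.7, and only if the effect is sustained.

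A reader might also say that any of three F tests could be called the result, or that baseline dilutes the whole analysis. The time effect does not compare arms, and the shrinkage applies to the between-subjects test alone. Baseline as a level of time is itself an inference, though the natural one.

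The authors do expect therapist differences, "because the present study is a multi-center trial employing the services of different treatment therapists with different skills and expertise". But the article describes no stratification by hospital, so no design factor is being dropped. A hospital term and any sphericity correction can be left to an analysis plan, and unequal spacing is no defect when time is categorical.

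An analysis plan that is not shown does not answer the central point. The article commits to this model, and the deciding comparison and its time point define the primary endpoint.

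**Conclusion.** The point holds in this form: two tests at 0.05 can each be read as the trial's answer, no visit is primary, and baseline IKHOAM is not used as a covariate. The inflation to about 0.098 needs no assumption about effect size. It assumes only that success on either test would be claimed, and it does not count any further choice among the four follow-up visits.

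The power loss is conditional. It is small if f = 0.47 holds at every follow-up. It is material if the effect is nearer 0.245, and for the between-subjects test it is severe if the effect appears at one visit only. The documents do not support saying that the planned ANOVA is underpowered as such, nor that 8 weeks is the correct primary visit, since no section ranks it above the others.

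**What to change.** Analyse the post-baseline IKHOAM scores with baseline IKHOAM as a covariate, either by ANCOVA or by a linear mixed model with arm, visit, arm by visit and baseline. Before unblinding, name one deciding arm comparison: either at one pre-named visit (end of treatment is one example) or on the average of the four post-baseline visits. The average has more power if the effect is sustained; a single visit is the better choice if the effect is expected to fade. Treat the remaining visits and the group by time test as secondary. Adjustment for hospital is optional.

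The cost is one degree of freedom for baseline, a change of wording, and the sponsor's commitment to one time point or average. No new data are needed. Recruitment has been open since February 2018 (Trial status), so the change should be dated and recorded before any data are seen by arm.
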